**Discussion:**

The innovative element of this intervention is the timing of the occupational rehabilitation which is much earlier initiated than usual and the active involvement of the workplace. We anticipate that vulnerable cancer survivors will benefit from this approach and reduce the effects of social inequality on workability.

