### Aim and hypotheses

The objectives are to apply an early, individually tailored occupational rehabilitation intervention to cancer survivors in two municipalities parallel with cancer treatment focusing on enhancing the R-RTW.

Two hypothesises;this early intervention conducted by a municipal job consultant will enhance the readiness for RTW and thereby increase the chance of RTW among cancer survivors from two municipalities compared with cancer survivors from municipalities not receiving this intervention but treated at the same hospital and receiving the standard municipal sick leave management.that socioeconomic status and/or co-morbidity will modify the effect of the intervention on RTW.

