### Sample size calculation

The sample size calculation is based on the primary outcome RTW.

Approximately 450 patients are annually referred to the oncology ward with the eligible cancer diagnosis of which 20 % reside in the two intervention municipalities. It is expected that the employment rate among cancer patients would correspond to that of the Danish background population equivalent to approximately 80 % [60]. Furthermore, it was anticipated that 80 % gave informed consent to participate in the study. Hence, an expected number of 288 cancer patients per year. We estimated a mortality rate of 10 % during the one-year follow-up. Based on previous studies the RTW rate among cancer survivors who underwent occupational rehabilitation is approximately 82 % [18], and that the share will be approximately 60 % in the control group [61, 62]. The hazard ratio (HR) is then given by: (HR: ln (40 %) / ln (18 %) = 1.87). With a power of 90 % and a significance level of 5 % a required sample size of 290 patients is needed. To obtain sufficient strength in the adjusted analyzes 250 survivors should RTW. Thus, the total number of cancer survivors required is 430 (of which 90 reside in the two intervention municipalities) which means an inclusion period of 1.5 years.

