### Statistical analyses

#### Primary outcome

The cumulative incidence proportion (CIP) as a function of the number of follow-up weeks is estimated using the Kaplan-Meier curve. The relative cumulative incidence of RTW within 52 weeks will be analyzed in a generalised linear regression model using the pseudo values method [63, 64].

Entry time is defined as the end of cancer treatment (identified from the hospital records) and the end of follow-up is 52 weeks following entry time. The outcome variable RTW consists of two measures: an event indicator (yes or no) and the time until RTW is identified in the DREAM register [65] or end of follow-up / competing risks (*early retirement benefit, retirement pension or death*)/censored observations (*emigration*), whichever comes first.

Adjustments for gender, age, cancer diagnosis, time since diagnosis and Charlson’s co-morbidity index [58] are going to be carried out. Moreover, analyses of whether socio-economic status or Charlson’s co-morbidity index modifies the effect of the intervention on RTW will also be carried out.

The significance level is set at p < 0.05. The results will be shown as crude and adjusted relative cumulative incidences, i.e. risks (RR) and corresponding 95 % confidence intervals (95 % CI).

STATA version 13.1 will be used as statistical software.

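### Effect modification by socioeconomic status and co-morbidity is assessed only as a ratio, which cannot by itself show whether the absolute social gap in return to work narrows

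*Protocol article*

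**What the plan says.** The second hypothesis, under Aim and hypotheses, is that "socioeconomic status and/or co-morbidity will modify the effect of the intervention on RTW". The Outcomes section makes this modification the secondary outcome. It takes socioeconomic status from Statistics Denmark and co-morbidity from the Charlson index.

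The Methods/Design paragraph of the abstract defines the effect as a relative cumulative incidence within 52 weeks. Its next sentence names co-morbidity and socioeconomic status as modifiers of that effect. The statistical section follows the same pattern: "The relative cumulative incidence of RTW within 52 weeks will be analyzed in a generalised linear regression model using the pseudo values method"; then "analyses of whether socio-economic status or Charlson’s co-morbidity index modifies the effect of the intervention on RTW will also be carried out"; then "The results will be shown as crude and adjusted relative cumulative incidences". No risk difference or other absolute contrast is named. One absolute quantity is planned, "The cumulative incidence proportion (CIP) as a function of the number of follow-up weeks is estimated using the Kaplan-Meier curve", but it is not tied to socioeconomic or co-morbidity strata and is not a measure of effect.

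Two further statements bear on the point. The abstract's background and the Background section describe social inequality in the chance of RTW and a harder RTW process in low socioeconomic groups. The abstract's discussion closes with an expectation: "We anticipate that vulnerable cancer survivors will benefit from this approach and reduce the effects of social inequality on workability".

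**The concern.** Whether an effect is modified is not a scale-free question. If two strata have different control rates and the intervention works in both, the ratio and the difference cannot both be constant. The article says that social groups start from different chances of RTW, so the choice of scale partly determines the answer to the secondary outcome.

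At stake is how the result will be read. A finding of no modification on the RR scale could be taken to mean that the intervention leaves the social gap as it was, and a larger RR in the low group could be taken to mean that the gap narrows. In percentage points, neither inference follows from the RRs alone.

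**Working it through.** **Inputs.** From Sample size calculation: RTW 82 % with occupational rehabilitation and 60 % in controls, 20 % of patients in the intervention municipalities, 10 % mortality, 430 patients in total with 90 in the intervention municipalities. Control RTW by stratum is not given. Assumption: two equal strata averaging 60 %, namely 55/65, 50/70 and 45/75 % (low/high).

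**The plan's own figures.** HR = ln(0.18)/ln(0.40) = 1.87 (the article prints this fraction inverted). With 90 % power, two-sided 5 % (sidedness assumed) and 20:80 allocation, the Schoenfeld formula gives 168 events. Mean RTW is 0.2 × 0.82 + 0.8 × 0.60 = 0.644. Then 168/0.644 = 261 and 261/0.9 = 290, as stated. For 250 events, 250/0.644/0.9 = 431, against 430 stated. Nothing below changes these sizes.

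**Effect on the two scales.** RR = 0.82/0.60 = 1.367. Risk difference = 0.82 − 0.60 = 22 points.

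**Effect of a common RR on the gap.** With control rates L < H and the same RR in both strata, the intervention gap is RR × H − RR × L = RR × (H − L). Any common RR above 1 multiplies the absolute gap by that RR.

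| Control low/high | Common RR 1.367: RTW | Gap, control → intervention | Common +22 points: RTW | RR low / high | Ratio of RRs |
|---|---|---|---|---|---|
| 55/65 % | 75.2/88.8 % | 10.0 → 13.7 | 77/87 % | 1.40/1.34 | 1.046 |
| 50/70 % | 68.3/95.7 % | 20.0 → 27.3 | 72/92 % | 1.44/1.31 | 1.096 |
| 45/75 % | 61.5/102.5 % (impossible) | – | 67/97 % | 1.49/1.29 | 1.151 |

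Under the common RR the ratio of RRs is 1.00 throughout. Under the common gain the gap stays at its control value.

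**A larger RR in the low stratum.** The gap narrows only if L(RR_L − 1) > H(RR_H − 1). At 50/70 %, RRs of 1.40 (low) and 1.30 (high) give 70 % and 91 %, so the gap is 21 points, slightly wider than 20. RRs of 1.45 and 1.30 give 72.5 % and 91 %, a gap of 18.5 points. Both patterns favour the low group as ratios, but only the second narrows the absolute gap.

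**Precision of the interaction.** Normal approximation, 430 patients, two equal strata, so 45 intervention and 170 control patients in each.

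- Ratio scale, 50/70 %, common +22 points: SE of the log ratio of RRs = √[0.28/(0.72 × 45) + 0.08/(0.92 × 45) + 0.50/(0.50 × 170) + 0.30/(0.70 × 170)] = 0.138. With ln(1.096) = 0.091, power is 10 %. Across the three assumed pairs it is 6 %, 10 % and 16 %.
- Difference scale, 50/70 %, common RR 1.367: SE = √[0.683 × 0.317/45 + 0.957 × 0.043/45 + 0.50 × 0.50/170 + 0.70 × 0.30/170] = 0.092. With a contrast of 0.073, power is 13 %. At 55/65 % it is 7 %. The 95 % interval has a half-width of about 1.96 × 0.092 = 0.18, or 18 points.

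With 387 patients (430 × 0.9) the figures are slightly lower: 6–15 % and 7–12 %.

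**The case against.** The strongest reply is that the RR answers the hypothesis as written. The hypothesis says only that the effect will be modified; it names no gap, direction or scale, and half of it concerns co-morbidity. Reduced inequality is an expectation in the abstract, worded in terms of work ability, with no test attached. Relative inequality is also a legitimate measure: under a common RR the low/high ratio of RTW stays at 50/70 = 68.3/95.7 = 0.71, so reporting no modification is correct on that scale. This stands. A reader might infer that the ratio gives the wrong answer, or that the second hypothesis is itself about narrowing the social gap. The documents support neither.

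A reader might also infer that RTW is so close to its ceiling that the RR is unusable. At 60 % control RTW the largest possible RR is 1/0.60 = 1.67. The planned RR is out of reach only in strata with control RTW above 1/1.367 = 73 %, and no stratum rates are given. The scale argument does not need a ceiling.

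A third reply is that an equal absolute benefit would rarely be declared modification at p < 0.05. That also stands, given the power above. It makes a report of no modification the likely outcome, and that report can accompany a widening absolute gap.

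Finally, link functions and stratum tables are details that a condensed article may leave to a fuller document, and the modification sentence itself names no scale. This carries less weight. The abstract defines the effect as a ratio and then speaks of modifying that effect, and the statistical section presents results as RRs. The ratio scale is therefore set by the text, although an additional scale elsewhere cannot be excluded.

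**Conclusion.** The point holds as a limit on what can be concluded, not as an error in the hypothesis or the primary analysis. The RR is the only effect measure named, and alone it cannot show whether the absolute social gap in RTW narrows. At the planned RR of 1.37, a common ratio widens any existing gap by 37 %: from 20 to 27 points at assumed control rates of 50 % and 70 %, and from 10 to 14 points at 55 % and 65 %. A uniform gain of 22 points shows as RRs of 1.44 and 1.31 at 50/70 %, with the gap unchanged.

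These sizes rest on assumed stratum rates in two equal strata. The direction rests only on control rates that differ and an RR above 1. Interaction precision is poor on both scales, so adding the difference improves interpretation but does not make the modification test informative.

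**What to change.** Keep the RR as planned. For the secondary outcome, also fit the same 52-week pseudo-value model with an identity link. Within each socioeconomic and co-morbidity stratum, report the 52-week RTW proportion in each group, the RR and the risk difference. Give the interaction contrast with its 95 % confidence interval on both scales: the ratio of RRs and the difference of risk differences. State in advance that any conclusion about inequality will be worded as relative or absolute according to the scale that supports it, and that estimates and intervals carry the interpretation, not the interaction p-value.

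The cost is one further link option in a model already planned and one table. The stratum variables are already to be taken from registers, and the sample size and primary analysis are unchanged. The drawback is that two scales are shown for one secondary outcome and may point in different directions, which is why the wording rule should be set before the data are analysed.

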### Ethical considerations

The study has been notified to and registered by the Danish Data Protection Agency (nr. 1-16-02-657-14). Approval from the Danish National Committee on Biomedical Research Ethics was not relevant as this is only provided for projects using biological material. Furthermore, the present study does not include biomedical treatment.

All patients provided informed consent prior to inclusion in the study.

## Discussion

This controlled trial uses the existing setting by which occupational/vocational rehabilitation takes place in Danish municipalities as of today. Already job consultants are appointed the role as case managers in cases of long-term sickness absence. Sick leave due to cancer is however, dealt with in different ways compared to less serious conditions; partly because of taboo, reluctance of discussing work with a potentially fatally ill absentee and off cause due to compassion for this person. However, the social security system, i.e. the Sickness Benefit Act and whether the cancer survivor is entitled to receive sickness benefit may not differentiate between the reasons for sick leave. As a consequence the cancer survivor may lose financial security while being sick-listed and also lose her or his job in the long run [7, 26, 27]. Moreover, the cancer survivor is left on her or his own to deal with these challenges, despite the fact that the majority of cancer survivors are motivated for and wishes to RTW [11].

The innovative element of this intervention is the timing and early onset of the occupational rehabilitation which is much earlier than usual and that the job consultants are articulating work and take action on the cancer survivors’ R-RTW and support them in behaviour change towards RTW. The evaluation of this intervention will point out if this approach in deed increases the RTW chance compared to the control municipalities.

The intervention will also be evaluated through qualitative interviews in terms of its acceptability to stakeholders and whether the existing setting is appropriate and whether job consultants are capable of this task.

The knowledge of RTW facilitators and barriers are quite extensive [2]. However, in the present trial it was not possible for us to take into account all of these factors. The cancer-related symptoms and possible disabilities due to treatment are not addressed directly within our intervention protocol. As the intervention takes place parallel with cancer treatment all of the cancer survivors are in contact with the health care system. If the job consultants identify health-related barriers in relation to RTW, they are intended to suggest the cancer survivor to get in contact with the treating oncologist or the general practitioner (GP). As well as the job consultants themselves can contact the health care professionals for advice.

According to the integrated cancer pathway “Rehabilitation and Palliation in Cancer” [16]; each municipality in Denmark is obliged to provide cancer rehabilitation. The municipal job consultants are well informed about the local offered rehabilitation within their municipality. Therefore we anticipate that health-related issues will be addressed because the healthcare stakeholders are close to the survivor and to the job consultants.

The theory behind our hypothesis that the intervention will increase RTW chance originates from the stages of change model [44]. The R-RTW model addresses the motivational factors of behaviour change towards RTW and maintenance of work and was validated in a population of claimants with muscular-skeletal disorders [40]. The scale has been translated to Norwegian and was validated in a Norwegian inpatient occupational rehabilitation program in sick-listed people [66]. The scale was reliable and a valid tool for the RTW prognosis.

In Denmark the R-RTW scale is currently being validated. The data from this study will be used in the validation of responsiveness. It was not possible to obtain R-RTW scores from the control group in this study. Thus, the scores obtained from the cancer survivors in the intervention group are used solely by the two job consultants to adjust their rehabilitation to the right stage.

### Methodological considerations

The golden standard when effects of an intervention are to be assessed is the randomised controlled trial (RCT) [18]. However, when studies are conducted in real settings, like in municipal job centres; recently published articles from the Danish national return-to-work program showed challenges in applying a randomised study design; i.e. spill over effects between study arms within the municipality [67–69]. Therefore we chose a controlled study design. When the control municipalities are to be chosen, high priority will be given to municipalities that resemble the RTW rate of the intervention municipalities the year before our study was initiated, i.e. 2013. For that purpose official rates from Statistics Denmark [57] will be used. We may not be able to identify municipalities which also can supply sufficient numbers of cancer patients fulfilling the inclusion and exclusion criteria. We might need to compromise on which municipalities to include as controls to get sufficient numbers of cancer survivors, which in turn might give residual confounding that will lower the internal validity of our results.

We believe that if the job consultants are to succeed in their support and help to the cancer survivors and thereby increase the R-RTW; they must identify barriers and facilitators in the RTW process and use the ACT inspired dialogue. Otherwise they may not be able to engage the cancer survivors in committed actions that are value-based and make sense to the survivors’ perception of quality of life (including work). In order for us to keep track of the compliance with the study protocol; the job consultants attend monthly supervisions with the psychologist who trained them in the use of ACT and IPS. Because the intervention takes place in the job consultants usual work setting, we fear that they are at risk of resuming old work habits and thereby violate the innovative elements in our intervention. We anticipate that the supervisions act as an arena where experiences are shared and difficult situations are discussed in order for the job consultants to learn and cope with their new job tasks and demands.

Due to the described intervention given by the job consultants it is not possible to blind the cancer survivors nor the job consultants or the person who will perform the analyses.

The sample size calculations are based on cancer survivors being sick-listed at entry time in the analyses. This means that we may need more than 430 cancer survivors in total. This might lead to a longer inclusion period than the anticipated 1.5 years. We anticipate that results will be available ultimo 2017.

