#### Control group

The control group is defined by patients with identical inclusion and exclusion criteria as the intervention group except that they live in other municipalities than Silkeborg and Randers.

The control group is identified via the electronic patient records at the Aarhus University Hospital.

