### Recruitment of the intervention group participants

Patients are recruited to the intervention group in a three-stage process:At each cancer ward a nurse or assistant nurse assigned to this project identifies patients living in Randers or Silkeborg municipality with the eligible cancer diagnosis.The treating oncologist is notified of this patient and at first given consultation the patient is informed about the project, is handed a written information sheet also containing an informed written consent formula. The patient is asked to read the information sheet and is informed that a municipal job consultant will contact the patient at home by phone.The municipal job consultant may also identify eligible patients even before cancer treatment has begun because of sick leave spells exceeding 8 weeks. In that case the treating hospital ward is notified about inclusion status; in that way no cancer survivor is asked twice about inclusion.Finally the patient is telephoned by the municipal job consultant, who thoroughly informs the patient about the project. Participation includes the patients’ willingness to involve next of kin, employer, and colleagues. If the patient accepts participation the first meeting is set up and the informed written consent formula is signed on that occasion.

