### Outcomes

#### Primary

The primary outcome is RTW among cancer survivors in the intervention group compared with the control group.

RTW is defined by at least 4 consecutive weeks of no social transfer payments or attending a modified job called “flexi job”.

The outcome is identified in a national register on weekly public transfer payments called the Danish Register for Evaluation of Marginalisation (DREAM) which has been found to provide valid information on labour market outcomes [55, 56]. Four consecutive weeks of no social transfer payments are considered to be equivalent to RTW along with four consecutive weeks of transfer payment equivalent to attending a “flexi job”.

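### The reason given for not blinding the analyst covers only patients and job consultants; the key variables can be derived and the code fixed before the analyst knows the true group

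*Protocol article*

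**What the plan says.** Under Methodological considerations, the article opens the blinding sentence with its reason, "Due to the described intervention given by the job consultants", and concludes that "it is not possible to blind the cancer survivors nor the job consultants or the person who will perform the analyses". No other reason is given for the analyst.

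The data that the analyst will use are described elsewhere:

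- **Outcome** (Outcomes, Primary): "The outcome is identified in a national register on weekly public transfer payments". The rule is explicit: "RTW is defined by at least 4 consecutive weeks of no social transfer payments", with flexi-job attendance also counted.
- **Time zero** (Statistical analyses, Primary outcome): "Entry time is defined as the end of cancer treatment (identified from the hospital records").
- **Socioeconomic status and co-morbidity** (Outcomes, Secondary): Statistics Denmark and the National Patient Registry.
- **Group** (Participants): municipality of residence. Controls come from hospital records: "The control group is identified via the electronic patient records at the Aarhus University Hospital". Intervention patients are approached on the ward or by job consultants, and consent in person.

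**The concern.** The statement of impossibility does not follow from its reason. Patients know what support they receive, and consultants know what they deliver. The analyst does neither and meets group only as a column in a dataset. As written, the sentence rules out a cheap safeguard.

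The safeguard has some value because the comparison is not randomised and some data steps need judgement. Entry time must be read from hospital records for patients who may have had surgery, radiotherapy or chemotherapy for any of several cancers, so the end of treatment may need interpretation. Patients are eligible whether working or sick-listed (Participants), while the sample size assumes that they are sick-listed at entry (end of Methodological considerations). Deciding who is sick-listed at entry therefore affects the at-risk set. If such decisions were made with group and outcome in view, they could shift the result in either direction, and the confidence interval would not show it.

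**Working it through.** **1. Which steps could be masked?** Setting the sections side by side:

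- *Choosing the cohort: no.* Intervention patients are recruited prospectively in two named municipalities. Controls are defined by living elsewhere, and their municipalities are still to be chosen. Group is the selection criterion.
- *Method, time point, measure, covariates, effect modifiers: masking adds little.* Statistical analyses already fixes a pseudo-value generalised linear model, 52 weeks, the relative risk, five adjustment covariates and the effect modifiers.
- *RTW: yes.* It is a fixed rule applied to weekly register data and does not need municipality. Little discretion remains here.
- *Sick-listed status at entry: yes.* Neither the entry date nor benefit status on that date requires group.
- *Covariate coding: yes.* Municipality is not among the listed covariates.
- *End-of-treatment date: yes in principle.* The records may show residence, and wards are told inclusion status when a job consultant has identified the patient, so masking may be imperfect.

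**2. Would a simple A/B code do?** The stated total is 430, of which 90 are in the intervention municipalities, so 430 − 90 = 340 are controls. The intervention share is 90/430 = 20.9%. Anyone tabulating A and B would see which is which. Randomly permuting the labels across patients keeps the 90:340 sizes, so the code can be tested, but breaks the link between label and outcome.

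**3. Does blinding affect the sample size?** No. The article's figures reproduce independently of it:

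- For 290: hazard ratio 1.87, two-sided 5%, 90% power and a 20% intervention share give 168 events by the Schoenfeld formula. Then 168 / (0.20 × 0.82 + 0.80 × 0.60) = 260.9, and 260.9 / 0.9 = 289.9.
- For 430: 0.9 × (90 × 0.82 + 340 × 0.60) = 250.0 events.

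**4. How much could the entry date matter?** The document gives no error rate, so this only illustrates scale. Assumptions: constant weekly RTW hazard, 60% RTW at 52 weeks in both groups (no true effect), and entry set *s* weeks too early in controls only, with no RTW in those extra weeks.

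- Hazard: λ = −ln(0.40)/52 = 0.0176 per week.
- Observed control proportion: 1 − exp(−λ(52 − s)).
- Spurious relative risk: 0.60 divided by that proportion.

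| s (weeks) | Observed control proportion | Spurious relative risk |
|---|---|---|
| 1 | 0.593 | 1.01 |
| 2 | 0.586 | 1.02 |
| 4 | 0.571 | 1.05 |
| 8 | 0.539 | 1.11 |

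The planned relative risk is 0.82/0.60 = 1.37. The same error in the intervention group only would give the reciprocal (for 4 weeks, 0.571/0.60 = 0.95), so the direction is not determined.

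**The case against.** The strongest reply is that an unblinded analyst applying a prespecified model to register data is not an error. The outcome rule leaves little to interpret, the main modelling choices are named, and the order of data steps belongs in an analysis or data-management plan that is not shown. Any bias here is minor beside the absence of randomisation and the open choice of controls, for which the article itself acknowledges possible residual confounding.

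Most of that stands, and it limits the point. It does not remove it, because the article does not leave the matter to a later plan: it says that blinding the analyst is impossible and gives a reason that does not apply to the analyst.

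A reader might infer more than the document supports:

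- *That the whole study file could be assembled blind.* It could not, because cohort selection is by municipality.
- *That the modelling is wide open.* It is not. Finer detail such as covariate coding may be settled in a plan not shown, and crude and adjusted results are both promised.
- *That the analyst will read treatment end dates knowing group and outcome.* The article does not say who abstracts these dates.
- *That the warning "We might need to compromise on which municipalities to include as controls" is part of the same problem.* It concerns which controls are selected, and masking the analyst would not change that.

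**Conclusion.** The point holds in a narrow form. The stated reason supports not blinding patients and job consultants; it does not support the claim about the analyst. The remaining discretion lies mainly in the end-of-treatment date and in who counts as sick-listed at entry, and to a lesser degree in covariate coding.

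The likely bias is small and neither its size nor its direction can be estimated from the document. The illustrative 1.01 to 1.11 rests on assumed one-sided shifts of 1 to 8 weeks and a constant hazard, and nothing in the article shows that such differential error will occur. No planned analysis is invalidated and no sample-size figure changes. This is an inexpensive improvement.

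**What to change.** Limit the statement of impossibility to patients and job consultants, and add a short data-handling commitment:

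- Entry date, sick-listed status at entry, RTW and covariates are derived on a file without the municipality variable. Items held only for intervention patients, such as readiness scores, are also kept off that file, because their presence would reveal group.
- Where feasible, residence is hidden from whoever reads the end-of-treatment date.
- Model code is written, tested and finalised with randomly permuted group labels, not an A/B code, because the planned 90:340 split would unmask the latter.
- True group is attached only once the derived variables and the code are fixed.

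If any of these steps cannot be done, the article should give a reason that applies to the analyst.

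The cost is a reordering of data steps and some programming time, with no change to sample size or patient contact. Masking of record reading may remain imperfect. The change does nothing about the choice of control municipalities or the lack of randomisation, which need separate handling.
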